#### Data extraction and mechanistic analyses

2.4.3

For each participant, we will derive:

SEA density and temporal distribution across nights and days.Within-subject variability in RAVLT learning, 30-min retention, and overnight consolidation.Sleep architecture metrics and spindle parameters.Day–night and day-to-day changes in plasma tau/Aβ.

SEA density will be correlated with memory performance, spindle metrics, and biomarker levels, as assessed using mixed-effects models that account for repeated measures. Comparisons will be made between SEA-rich and SEA-poor epochs and between days with high vs low hyperexcitability burden. Group-specific patterns (e.g., MCI vs ASD vs ADHD) will be examined.

### Data management and quality assurance

2.5

A detailed data management plan governs:

Standardized naming conventions and metadata.Secure storage of pseudonymized data on institutional servers with routine backup.Separation of personal identifiers from research data; access limited to authorized staff.Harmonized SOPs for acquisition and preprocessing of EEG, MRI, and biomarker data.

Quality control steps include:

Visual inspection of MRI segmentations and fMRI registrations.Inter-rater agreement for EEG interpretation (SEA detection) and sleep staging is formally evaluated using Cohen’s κ coefficient (with 95% confidence intervals) before consensus adjudication. Periodic calibration sessions are conducted throughout the study to maintain consistency in scoring across raters, and periodic auditing of neuropsychological scoring is conducted.Data-integrity milestones (EEG, neuroimaging) with open-source anonymized libraries planned for selected datasets.

Pseudo-anonymized datasets and analysis scripts will be made available to qualified investigators upon reasonable request, in line with ethical and legal frameworks, and will support future meta-analyses.

### Statistical analysis

2.6

#### Cross-sectional analyses

2.6.1

Data from all diagnostic groups will be pooled into a single multivariate dataset and analyzed using machine learning and dimensional reduction techniques to extract cross-diagnostic patterns of neural and behavioral variance. The model will test for latent factors reflecting shared E/I imbalance across disorders, while *post hoc* analyses identify disorder-specific deviations. Statistical adjustments will account for confounders such as age, medication, and cognitive status.

Primary outcome will be the (Torenvliet et al., 2023) incidence and distribution of SEA, and fMRI hyperactivity in each diagnostic group relative to controls. Secondary outcomes will include relationships between hyperexcitability and (a) structural atrophy and white matter integrity; (b) functional connectivity within and between default mode, salience, and attention networks; (c) CSF and plasma tau/Aβ levels; and (d) domain-specific cognitive performance.

Incidence of hyperexcitability (primary outcome):○Logistic regression models comparing SEA and fMRI-positive status between groups (MCI, ASD, ADHD vs HC), adjusting for age, sex, education, and disease duration where applicable.○Results will be reported as odds ratios with 95% confidence intervals.

Associations with cognition, structure, and connectivity (secondary outcomes):○Within each group, participants will be classified as hyperexcitability-positive vs negative (see section “2.4.1 Participant selection and extraction of normative values”).○For continuous outcomes (neuropsychological scores, cortical thickness/volume, DTI measures, functional connectivity indices, blood-based biomarker concentrations), group comparisons will use *t*-tests or Mann–Whitney U tests depending on normality (Shapiro-Wilk).○For categorical variables, chi-square tests will be used.○Multivariable linear models with covariates (age, sex, education, disease duration, mood/anxiety scores) will assess independent associations.Holm–Bonferroni corrections will be used to control for multiple comparisons.

Cross-modal relationships:○Correlation and regression analyses will examine relationships between spike density and fMRI hyperactivity.○Multimodal latent variable models or clustering approaches will be applied exploratorily to define hyperexcitability phenotypes.

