**Anticipated results:**

Primary outcome is the incidence and distribution of cortical hyperexcitability in each diagnostic group relative to controls. Secondary outcomes include relationships between hyperexcitability and (a) structural atrophy and white matter integrity; (b) functional connectivity within and between default mode, salience, and attention networks; (c) cerebrospinal and plasma tau/amyloid levels; and (e) domain-specific cognitive performance. The current paper describes the study design, while the results are not reported.

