**Incidence of cortical hyperexcitability.**
*Hypothesis 1:* The incidence of cortical hyperexcitability (SEA on EEG, network-specific hyperactivity on resting-state fMRI) is significantly higher in MCI, ASD, and ADHD than in cognitively healthy controls.

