#### Sample size justification

2.2.4

Power calculations for the primary cross-sectional study were informed by previous investigations of cortical hyperexcitability and subclinical epileptiform activity (SEA) in neurocognitive disorders [summarized by Horvath et al. (2020)]. Assuming a medium effect size (Cohen’s *d* = 0.5), a two-sided significance level of α = 0.05, and four diagnostic groups, a sample size of 75 participants per group (total *N* = 300) provides more than 90% power to detect clinically meaningful between-group differences in the primary outcomes, including the incidence of SEA and resting-state fMRI hyperactivity.

The mechanistic in-ward substudy is enrichment-based and will include participants demonstrating evidence of cortical hyperexcitability. Assuming a conservative prevalence of approximately 15% across the clinical groups, we anticipate recruiting approximately 45 eligible participants, with an expected final sample of approximately 40 after accounting for an estimated 20% attrition rate.

The mechanistic substudy is designed primarily to characterize within-subject physiological relationships among cortical hyperexcitability, sleep architecture, memory consolidation, and circulating biomarkers using repeated-measures analyses. Because repeated observations substantially increase statistical efficiency for within-subject comparisons, this sample size is considered appropriate for estimating effect sizes, assessing feasibility, and identifying candidate mechanistic pathways. In contrast, more analytically demanding models, including formal mediation analyses and subgroup comparisons across diagnostic categories, are expected to have limited statistical power with the anticipated sample size. Accordingly, these analyses will be considered exploratory and hypothesis-generating, with emphasis placed on effect size estimation, confidence intervals, and model uncertainty rather than statistical significance alone. Findings from these exploratory analyses will inform sample size calculations and analytic strategies for future confirmatory multicenter studies.

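### The plan does not say whether Holm–Bonferroni covers the six primary contrasts or how many must succeed for Hypothesis 1, and the stated power above 90% does not describe those contrasts

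*Protocol article*

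**What the plan says.** - **Hypothesis (1.2).** Hypothesis 1 says that the incidence of hyperexcitability, meaning SEA on EEG and network hyperactivity on fMRI, "is significantly higher in MCI, ASD, and ADHD than in cognitively healthy controls".
- **Outcome.** The abstract uses one umbrella term: "Primary outcome is the incidence and distribution of cortical hyperexcitability in each diagnostic group relative to controls". Section 2.6.1 names SEA and fMRI hyperactivity, each in every diagnostic group relative to controls.
- **Primary analysis (2.6.1).** "Logistic regression models comparing SEA and fMRI-positive status between groups (MCI, ASD, ADHD vs HC", adjusted for covariates and reported as odds ratios with 95% confidence intervals.
- **Multiplicity (2.6.1).** "Holm–Bonferroni corrections will be used to control for multiple comparisons". The sentence comes at the end of the block on secondary outcomes. It names no family and does not mention the primary odds ratios.
- **Sample size (2.2.4).** The calculation takes a standardised difference of 0.5 with "a two-sided significance level of α = 0.05, and four diagnostic groups". From this the article concludes that "a sample size of 75 participants per group (total *N* = 300) provides more than 90% power". The claim is said to apply to several outcomes at once: "between-group differences in the primary outcomes, including the incidence of SEA and resting-state fMRI hyperactivity".

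**The concern.** Three diagnoses, each compared with one control group on two binary statuses, make six primary contrasts. As the text is placed, the secondary comparisons are corrected and the primary ones are not. No contrast or modality is named as deciding.

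Suppose only one of the six is significant, for example fMRI status in ADHD. One analyst could report Hypothesis 1 as supported and another as not supported, both following the text. One could apply Holm to the six and the other could leave them at 0.05. The transdiagnostic conclusions in section 3.2 rest on these contrasts.

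The power statement adds to the difficulty. It gives one figure for the primary outcomes without saying which test or success rule it refers to.

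**Working it through.** **Inputs.** From 2.2.4: d = 0.5, two-sided α = 0.05, 75 per group, four groups, N = 300. From 2.6.1: six contrasts. Contrasts sharing a control group of equal size have correlation (1/75)/(2/75) = 0.5. The correlation between SEA and fMRI status is not given. I assume 0 to 0.8, since Hypothesis 5 expects it to be positive.

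**1. The plan's power figure.** A four-group omnibus F test with f = d/2 = 0.25 has noncentrality 300 × 0.25² = 18.75 on 3 and 296 df. Power is 96.4%, consistent with the statement. This needs two groups at one mean and two at another. If controls alone differ from three equal patient groups, f = 0.5 × √3/4 = 0.217 and power is 89.3%. With the two middle groups halfway between the extremes, f = 0.5/√8 = 0.177 and power is 72.4%.

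**2. Power of the listed contrasts.** The expected z is d√(n/2) = 0.5 × √37.5 = 3.062.

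- At 0.05: Φ(3.062 − 1.960) = 86.5% (noncentral t: 86.0%).
- At 0.05/6 = 0.00833, the hardest Holm step: Φ(3.062 − 2.638) = 66.4% (noncentral t: 65.1%).
- One-sided pairwise power is 92.2%, but the plan states a two-sided level.

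Simulating six correlated normal statistics, each with mean 3.062:

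- All three diagnoses significant in one modality: about 72%.
- All six significant: 51% (modality correlation 0) to 63% (0.8).
- Holm over six, average power per contrast if all six effects are real: about 77%.
- Holm over six, at least one significant if all six effects are real: 93–98%.

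**3. The effect scale.** d = 0.5 is a continuous-scale effect, while the outcomes are binary. The arcsine analogue, 2·asin√p₁ − 2·asin√p₀ = 0.5, with assumed control rates of 2% to 15% (patient rates 14.6% to 36.4%), gives 80–86% power at 0.05 and 56–65% at 0.05/6.

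**4. False positives if the six contrasts are uncorrected.** With independent tests, 1 − 0.95⁶ = 26.5%. With the shared control group (simulation of normal statistics under the null):

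| Modality correlation | Any two-sided false positive | Any false finding of higher incidence |
|---|---|---|
| 0 | 23.6% | 12.1% |
| 0.3 | 22.9% | 11.6% |
| 0.5 | 21.9% | 11.0% |
| 0.8 | 19.0% | 9.5% |

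The single-test references are 5% and 2.5%. Testing all six at 0.05/6 brings the two-sided figure to 3.8–4.5%.

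**5. Binary data.** With 75 per group, unadjusted models, independent modalities and a common positive rate of 15–30%, the two-sided figure is 21–24%. At 5% in both modalities it depends on the test: about 5% with Wald and 32% with likelihood-ratio tests. With SEA at 5% and fMRI at 20%, Wald gives 14%.

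**The case against.** - **A correction is in the plan.** The Holm sentence names no family and excludes none. In the extracted text it lacks the sub-bullet mark of the items before it, so it may be a general statement for the section. If it covers the six contrasts, family-wise error is at most 5%. This stands: a reader might infer that every primary test is run at the full 5%, but the document does not say so.
- **Hypothesis 1 is directional.** A false finding of lower incidence cannot support it. This stands: a flat claim of a 20% chance of a false primary conclusion would count both directions, and the relevant figure is about half that.
- **The hypothesis can be read as requiring all three diagnoses.** Testing each at 5% then does not inflate the error of the joint claim. This stands for error, but on that reading power is about 72% in one modality.
- **Low positivity rates reduce the error under Wald tests.** Section 2.4.1 sets the SEA limit at the 95th percentile of controls, which suggests roughly 5% positive under the null. This stands as a limit on the size.
- **The abstract's single term is not a contradiction.** Hypothesis 1 defines it by the two markers. This stands.
- **The power could mean at least one success.** If all six effects are real, that chance exceeds 90% even under Holm. The plan states no such rule, and the figure says nothing about a given diagnosis.
- **An analysis plan usually settles such detail, and the study is observational.** This lowers the weight. It does not remove the point: the article itself states a correction, places it under the secondary outcomes, and gives a power figure that does not match the listed analysis.

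**Conclusion.** The concern holds in limited form. The article sets six primary contrasts with ordinary 95% intervals, leaves the reach of Holm–Bonferroni open, and gives no success rule for Hypothesis 1.

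The false-positive figures of 19–24% (two-sided) and about 10–12% (higher incidence only) rest on two conditions: Holm does not cover the primary contrasts, and any single success counts. They also assume approximately normal test statistics and a modality correlation of 0 to 0.8. Under those conditions the inflation is roughly four- to fivefold in either column. It disappears if Holm applies to the six or if all must succeed.

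The power point does not depend on how Holm is read. At the plan's own inputs no two-sided pairwise contrast reaches 90%, with about 86% uncorrected and 65% at the hardest Holm step. The all-succeed rules give 72% and 51–63%. The figure is matched by an omnibus test that 2.6.1 does not list as the primary analysis. These powers are illustrative, because d = 0.5 is not a difference in positive rates. For an observational study that reports all its odds ratios, this should be clarified before the comparisons are made, but it does not undermine the design.

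**What to change.** In 2.6.1, state that Hypothesis 1 is judged separately for each diagnosis-by-modality contrast, and that the Holm procedure already in the plan is applied to the six primary contrasts at two-sided family-wise 0.05. A family per modality, or a rule that all must succeed, would also be defensible. What matters is that one rule is written down before the groups are compared.

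In 2.2.4, restate the power for the pairwise contrasts at the level used, and note that d = 0.5 is a continuous-scale effect while the outcomes are binary. Assumed positive rates in controls and patients would be a better basis.

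The cost is a few sentences and a less favourable stated power: about 65% at the hardest Holm step, and about 77% on average per contrast if all six effects are real. No new data are needed. If the sponsor wished to keep 90% at 0.05/6 for d = 0.5, about 123 per group would be required (97 for 80%), but the fix does not depend on enlarging the study.

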All recordings will be independently reviewed by two experienced clinical neurophysiologists who are blinded to diagnosis and other clinical information. Epileptiform discharges will be accepted only when both reviewers reach consensus. Prior to consensus adjudication, inter-rater agreement will be quantified using Cohen’s κ coefficient for the presence or absence of subclinical epileptiform activity, with κ values and 95% confidence intervals reported in the final study results. Discordant cases will be reviewed jointly to establish the final classification. Automated spike detection (Persyst) will serve as a supporting tool for quantifying spike density, amplitude, and duration, while all final classifications remain based on expert visual assessment. The average spike density (spikes/hour) will be computed, and scalp distribution will be categorized (frontal, temporal, parietal, occipital, etc.) using Micromed SystemPLUS 98. Participants will be labeled as EEG-positive or negative for SEA relative to HC normative values obtained from our reference database (ACOL). The SEA detection pipeline is reported in our previous publications (Horváth et al., 2018b; Horvath et al., 2021).

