#### Participant selection and extraction of normative values

2.4.1

Across all groups (HC, MCI, ASD, ADHD), participants with clear evidence of cortical hyperexcitability—defined by at least one of: SEA on EEG above a predefined density threshold; or fMRI-defined hyperactivity in DMN/SN/AN—are invited to participate. We will initially prioritize HC and MCI subjects during the pilot phase to refine the in-ward protocol, then extend to ASD/ADHD.

Normative values for the fMRI and EEG metrics will be calculated using the ACOL dataset. The ACOL dataset is our clinical registry, founded in 2014, and contains longitudinal data from 500 individuals at various stages of the cognitive continuum. The dataset includes 280 healthy individuals (mean age = 55) with records on clinical anamnesis, demographics, blood-based biomarkers, neurological examination, medications, neuropsychology, 24-h Holter-EEG, 10-min resting EEG, sMRI, 10-min resting fMRI, pupillometric data, fine-movement analysis, and autonomic functions. All participants have been scanned with the same MRI scanner (Siemens Magnetom 3T) and examined with the same EEG recording system (Micromed Morpheus Holter-EEG). Further details on the dataset can be found at the EuroFingers Consortium website^1^.

To generate normative fMRI values, we perform rigorous preprocessing of all scans—motion correction, spatial normalization, smoothing, and signal denoising—to ensure comparability across individuals. Next, functional metrics, including functional connectivity strength, regional homogeneity (ReHo), amplitude of low-frequency fluctuations (ALFF), Hurst-exponent, and network efficiency, are extracted for each subject. Within the healthy control group, these measures are then aggregated and standardized by computing the mean and standard deviation of each metric across all participants to generate z-score distributions that define the “normal” range. Statistical modeling (Gaussian mixture) is used to identify normative intervals and detect outliers. To account for biological variability, the dataset is stratified by relevant covariates such as age, sex, and head motion. The resulting normative models can then serve as a statistical reference framework, allowing patient metrics to be expressed as deviation scores (z-scores) that quantify brain abnormalities relative to typical controls.

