To generate normative EEG values, we perform meticulous EEG preprocessing on 24-h recordings—artifact removal (e.g., eye blinks, muscle noise), filtering, and referencing—to ensure clean data. Two manual expert reviews of the files to identify potential SEA in line with the previously published protocols (Kamondi et al., 2024; Port et al., 2019). To define normal limits, the density, amplitude, duration, and spatial distribution of these events can be quantified across all control recordings. Statistically, normal values are represented by upper tolerance limits (the 95th percentile) of spike density (events per hour) computed from the control group. Normative modeling is applied to further refine these thresholds by accounting for age, sex, sleep state, and recording montage, variables known to influence EEG background and transient patterns. Additionally, spectral power and band ratios (delta, theta, alpha, beta, gamma) are used to construct normative baselines, against which epileptiform spikes produce transient deviations.

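### The sample size rests on a mean shift of d = 0.5, but the primary analysis compares only positive/negative labels; the claimed power above 90% does not carry over

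*Protocol article*

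**What the plan says.** Both markers are measured on a graded scale and then reduced to labels.

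- **EEG.** Section 2.3.4: "The average spike density (spikes/hour) will be computed". Participants are then labelled EEG-positive or EEG-negative against reference norms. Section 2.4.1 gives the limit: "normal values are represented by upper tolerance limits (the 95th percentile) of spike density (events per hour) computed from the control group".
- **fMRI.** Section 2.4.1 describes a reference framework "allowing patient metrics to be expressed as deviation scores (z-scores) that quantify brain abnormalities relative to typical controls". Section 2.3.3 classifies participants as fMRI-positive or fMRI-negative, where positive means significantly elevated against control norms. No z-value or percentile is given.
- **Primary analysis.** Section 2.6.1 names the incidence and the distribution of both markers as the primary outcome. The only group analysis listed for it is "Logistic regression models comparing SEA and fMRI-positive status between groups (MCI, ASD, ADHD vs HC), adjusting for age, sex, education, and disease duration", reported as odds ratios with 95% confidence intervals. Continuous spike density enters the cross-modal and mechanistic analyses, not the primary group comparison.
- **Sample size.** Section 2.2.4: "Assuming a medium effect size (Cohen’s *d* = 0.5), a two-sided significance level of α = 0.05, and four diagnostic groups", and "a sample size of 75 participants per group (total *N* = 300) provides more than 90% power to detect clinically meaningful between-group differences". The outcomes that section names are the two incidences. It gives no positivity rate per group as a power input.

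**The concern.** Cohen's d is a difference in means in SD units. It describes a comparison of spike density or z-scores on their own scale, whereas the planned test compares two proportions. A cut far into the upper tail uses little of a modest shift in the whole distribution, so the power of the two tests can differ widely under one and the same effect.

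At stake is Hypothesis 1. If patients shift moderately as a group, the study could report no excess hyperexcitability although the spike densities and z-scores it collected would show one. Readers would also take a null result as coming from a study with more than 90% power.

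**Working it through.** **Inputs.** d = 0.5, two-sided alpha 0.05, four groups, 75 per group (2.2.4); EEG limit at the control 95th percentile (2.4.1); logistic contrasts of each patient group with healthy controls (2.6.1). Assumed here: a normal marker, a uniform shift of 0.5 SD, no covariates, and controls that match the reference norms.

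**1. The plan's figure.** A one-way ANOVA with four groups, N = 300 and f = 0.25 (the usual counterpart of d = 0.5) has 96.4% power. This fits the claim of more than 90%, but it is a test on a continuous outcome that 2.6.1 does not plan. With all three patient groups 0.5 SD above controls, f = 0.217 and power is 89.3%.

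**2. One contrast, full scale.** 0.5 × √(75/2) = 3.06, and Φ(3.06 − 1.96) = 86.5%. The noncentral t gives 86.0%.

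**3. One contrast, labels cut at the control 95th percentile.**
- Controls positive: p0 = 0.05.
- Patients positive: p1 = 1 − Φ(1.645 − 0.5) = 0.126.
- Pooled SE = √(2 × 0.088 × 0.912 / 75) = 0.0463. Unpooled SE = √((0.05 × 0.95 + 0.126 × 0.874) / 75) = 0.0459.
- Power = Φ((0.0761 − 1.96 × 0.0463) / 0.0459) = Φ(−0.32) = 37.5%.

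| Method | Power |
|---|---|
| Normal approximation, pooled / unpooled | 37.5% / 38.2% |
| Exact chi-square | 38.9% |
| Logistic, likelihood ratio | 39.8% |
| Logistic, Wald | 30.2% |
| Fisher | 27.8% |

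For 90% power the label test would need 290 per group; the full-scale test would need 85.

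**4. Other cuts, for fMRI.** The same calculation by assumed control cut:

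| Cut | Median | 80th | 85th | 90th | 95th | 97.5th | z > 2 |
|---|---|---|---|---|---|---|---|
| Power | 67% | 62% | 58% | 50% | 38% | 27% | about 25% |

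**5. Many zero spike densities.** The share of zeros is not in the document. With 50%, 70%, 80% and 90% of controls at zero and the same latent shift in every patient, simulated Mann-Whitney power is about 80%, 73%, 67% and 51%, against 39% for the label.

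**6. Only a subgroup affected.** Assume that 15% of patients shift by 3 SD and the rest match controls. Patients positive: 0.15 × 0.912 + 0.85 × 0.05 = 0.179. Simulated power is about 73% for the label test. For Mann-Whitney it is about 34%, 37%, 52% and 65% with 0%, 50%, 80% and 90% of controls at zero. With 20% affected, it is about 90% for the label test against roughly 55% to 85%.

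**7. Power by positivity rate.** With 5% of controls positive, the pooled normal approximation gives 53% for 15% positive in patients, 80% for 20% and 94% for 25%.

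**The case against.** The strongest reply is that incidence is the question asked. Hypothesis 1, the abstract and 2.6.1 all ask whether hyperexcitability is more frequent, and a test of degree answers something else. SEA is also a clinical reading: two blinded readers decide by consensus, κ is computed for its presence or absence, and automated density has only a supporting role. This stands, and it is a good reason to keep the logistic models.

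The second reply is that a uniform shift is one model among several. The protocol often speaks of an affected subset, and under step 6 the label test beats the rank test. This also stands. A reader might infer that dichotomising is simply wrong and that a graded test should replace the label test. The documents do not support that, because they state no distribution and the sign of the gain depends on it.

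The third reply is that graded data are used elsewhere. That is true of the cross-modal and mechanistic analyses. The voxel-wise ANCOVA in 2.3.3 contrasts seed-connectivity maps and does not cover spike density. None of these is the primary group comparison.

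None of the three rescues the power statement, which names incidences and supports them with a mean difference.

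**Conclusion.** The point holds as a mismatch between 2.2.4 and 2.6.1. Under the plan's own d = 0.5, read as a uniform shift of a normal marker and cut at the one limit the protocol states, the EEG label contrast has about 38-39% power (28-30% by Fisher or Wald), not more than 90%. The full-scale contrast has 86%.

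Two further readings are tempting and go too far. The 39% does not apply to both markers: the 95th percentile is given only for spike density, and for fMRI the range is about 25-67% by assumed cut. Nor is the claim of more than 90% an arithmetic slip, since it reproduces as a four-group ANOVA; it belongs to a different test. Actual power for incidence depends on positivity rates that the protocol does not give per group, and it would be adequate if patients reached 20-25% against 5% in controls.

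**What to change.** **Section 2.6.1.** Keep the logistic models and odds ratios for incidence. Add a pre-specified graded comparison of each patient group with healthy controls, as co-primary or key supporting analysis of the distribution part of the outcome:
- spike density with zeros kept as the lowest rank, by ordinal (proportional-odds) regression;
- one fMRI deviation z-score, named in advance, by linear regression;
- both adjusted for age, sex and education.

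If the graded comparison is co-primary, extend the Holm-Bonferroni correction, now listed with the secondary outcomes, to cover it.

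**Section 2.2.4.** Replace the claim of more than 90% with power for the label contrasts at stated positivity rates, for example the three rates in step 7. Give the d = 0.5 figure (86% per contrast at 0.05, before any multiplicity correction) only for the graded comparison.

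**Cost.** Two more models, the need to choose one fMRI metric in advance, and a less favourable stated power. No new data or participants are needed.

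### The primary SEA logistic model probably rests on about four positive controls; a Firth penalised fit would be a cheap improvement on the default fit

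*Protocol article*

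**What the plan says.** Section 2.6.1 defines the primary analysis as "Logistic regression models comparing SEA and fMRI-positive status between groups (MCI, ASD, ADHD vs HC"), adjusted for age, sex, education and, where it applies, disease duration. It continues: "Results will be reported as odds ratios with 95% confidence intervals". It does not say whether the fit is ordinary maximum likelihood or penalised, or what type of interval is used.

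EEG status is assigned relative to healthy norms from the ACOL registry (section 2.3.4), which holds 280 healthy individuals (section 2.4.1). Section 2.4.1 sets the EEG limit: "normal values are represented by upper tolerance limits (the 95th percentile) of spike density (events per hour) computed from the control group". These limits are then refined for age, sex, sleep state and montage.

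fMRI positivity is defined by elevation over ACOL norms in three networks (sections 2.3.3 and 2.4.1), with no numerical cut-off.

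Section 2.2.4 fixes "a sample size of 75 participants per group". Its power statement uses a standardised mean difference and gives no event rates.

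**The concern.** A cut-off at the 95th percentile of healthy people makes positivity rare in healthy controls by design. With 75 controls, the reference cell of the SEA model is then likely to hold only a handful of events, and all three primary SEA contrasts share it.

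Ordinary maximum-likelihood logistic regression behaves poorly with such a cell. The odds ratio is biased away from 1, which here is the direction of Hypothesis 1. It has no finite value if no control is positive. Wald inference also loses power. If the control count came out at zero, the promised odds ratios and intervals could not be produced for any SEA contrast by the default method, and a remedy would have to be chosen after seeing the data.

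**Working it through.** **The plan's own figure.** The article states no control event count, so there is none to reproduce. Its only related figure is the power claim in section 2.2.4, which is built on d = 0.5. A pairwise comparison of 75 with 75 at two-sided 0.05 gives 86.5%, and an omnibus test with f = 0.25 gives 96.4%. Neither calculation contains an event rate, and nothing below depends on them.

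**Inputs**
- Controls: n = 75 (section 2.2.4).
- Control SEA rate p0: about 5%, inferred from the 95th-percentile limit (section 2.4.1). This is an assumption, so a range is shown.
- Clinical-group rate p1: 15%. Section 2.2.4 uses it for hyperexcitability in the clinical groups when sizing the substudy. It covers SEA or fMRI positivity, so it is borrowed here.

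**Expected control events and empty cells.** Expected events = 75 × p0, and P(none) = (1 − p0)^75.

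| p0 | Expected | P(0) | P(0 or 1) |
|---|---|---|---|
| 2% | 1.5 | 22% | 56% |
| 3% | 2.25 | 10% | 34% |
| 5% | 3.75 | 2.1% | 10.6% |
| 10% | 7.5 | 0.04% | 0.3% |

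**Events and parameters.** At 5% and 15%, total events = 3 × 11.25 + 3.75 = 37.5. The model has 7 parameters: intercept, three groups, age, sex and education.

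**Bias at 5% versus 15%.** True odds ratio = (0.15/0.85)/(0.05/0.95) = 3.35.
- Unadjusted, by exact binomial summation: given a finite estimate, the mean log odds ratio is too high by 0.07 under maximum likelihood and by 0.00 under Firth (0.5 added to each cell).
- Adjusted, 1,500 simulated studies with assumed covariate distributions: the maximum-likelihood bias is +0.08 to +0.12 across the three contrasts, with no finite estimate in about 2% of studies. Firth bias is −0.02 to +0.01, and every fit is finite. Coverage of the 95% interval is 96–97% for both.
- A separate adjusted simulation with its own assumed covariates gave a maximum-likelihood bias of about +0.05, with no estimate in about 2.5% of studies.
- On the odds-ratio scale, exp(0.05) = 1.05 and exp(0.12) = 1.13, hence 5–13% too high.

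**Power of the test.** In that second simulation the Wald test rejected in 46% of studies and Firth with profile penalised likelihood in 52%. With a control rate of 3% the figures were 61% and 75%.

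**Conservatism under the null.** For the unadjusted 2×2 table, summing binomial probabilities over all tables that reject, with p0 = p1 = 5% and tables with an empty cell counted as non-rejections under Wald, gives a true level of about 1.0% for Wald and 3.3% for the Firth profile test. The extra power therefore does not come from exceeding 5%.

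**Bias at a 2% control rate (versus 15%).** Maximum likelihood has no finite estimate in about 20% of adjusted simulations. Firth is always finite, with a log-odds-ratio bias of −0.06 unadjusted and −0.08 to −0.10 adjusted.

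**What no estimator repairs.** At the expected counts, SE(log OR) = √(1/3.75 + 1/71.25 + 1/11.25 + 1/63.75) = 0.62. Since exp(1.96 × 0.62) ≈ 3.4, an interval around 3.35 runs from about 1 to about 11.

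**fMRI.** If any of k independent measures above its own 95th percentile counted as positive (an assumption), expected positive controls = 75 × (1 − 0.95^k): 3.75 for k = 1, 10.7 for k = 3, 19.9 for k = 6. The document does not say which applies.

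**The case against.** The strongest reply is that the article makes no mistake here. It says logistic regression with odds ratios and 95% intervals, and a Firth fit with profile intervals satisfies that wording. The choice of estimator and the handling of sparse cells commonly belong in an analysis plan, which is not shown. This stands: the point is an improvement to specify, not an error in the text, and a reader should not infer that the article commits to maximum likelihood or Wald intervals.

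The harm is also small in the base case. A bias of 0.07 on the log scale is about a tenth of the standard error (0.07/0.62 = 0.11), and coverage is not below nominal. This stands too. It would be wrong to conclude that the default intervals are generally invalid.

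The 5% is not fixed by construction in the study controls. The cut-off comes from another sample and is then refined. One might argue that screening controls for normal MRI, cognition and laboratory tests lowers their rate, but the article gives no figure for this and the ACOL reference subjects are healthy as well. The 2% and 3% rows are a sensitivity range, not predictions.

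Finally, Firth does not cure a chance deficit of control events. With 11/75 positive patients and 0/75 controls, the unadjusted Firth odds ratio is (11.5/64.5)/(0.5/75.5) = 26.9. With 1/75 controls it is (11.5/64.5)/(1.5/74.5) = 8.9, against (11/64)/(1/74) = 12.7 by maximum likelihood. Both Firth values are finite but far above 3.35. This limits what the fix can claim. It does not remove the gain in bias, existence of the estimate and power.

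**Conclusion.** The point holds as a low-cost improvement to the primary SEA model. The article's cut-off, group size and choice of reference together imply about 3.75 SEA-positive controls behind all three SEA odds ratios, provided the study controls resemble the ACOL healthy reference. If the default fit is used, the consequences at 5% versus 15% are an upward shift of roughly 5–13% in the odds ratio, about a 2% chance of no finite estimate, and a conservative test. The chance of no finite estimate rises to 10% and 22% at control rates of 3% and 2%.

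A reader might infer that the whole primary analysis, fMRI included, rests on four control events. The document does not support that: without a numerical fMRI cut-off, the fMRI control count cannot be derived and could be several times larger. The simulation figures also depend on assumed covariate distributions and on a 15% clinical rate that the article states for SEA or fMRI positivity combined.

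**What to change.** In section 2.6.1, state that the primary SEA model will be fitted by Firth penalised likelihood with profile penalised-likelihood 95% confidence intervals, and that the fMRI model will be fitted the same way if its control cell proves similarly sparse. Beside the odds ratios, report the prevalence difference of each clinical group from controls with score-type intervals. These remain defined when no control is positive and add a between-group measure to the incidence by group that is already planned.

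The cost is analysis wording only, with standard software and no change to design or data collection. The downsides are slight shrinkage of estimates towards 1 and a small downward bias if the control rate is near 2%. The write-up should still say plainly that precision is limited by the number of positive controls.
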